# Temporary transvenous diaphragm pacing vs. standard of care for weaning from mechanical ventilation: study protocol for a randomized trial

**DOI:** 10.1186/s13063-018-3171-9

**Published:** 2019-01-17

**Keywords:** Mechanical ventilation, Weaning, Diaphragm, Ventilator-induced diaphragmatic dysfunction, Phrenic stimulation

## Abstract

**Background:**

Mechanical ventilation (MV) is a life-saving technology that restores or assists breathing. Like any treatment, MV has side effects. In some patients it can cause diaphragmatic atrophy, injury, and dysfunction (ventilator-induced diaphragmatic dysfunction, VIDD). Accumulating evidence suggests that VIDD makes weaning from MV difficult, which involves increased morbidity and mortality.

**Methods and analysis:**

This paper describes the protocol of a randomized, controlled, open-label, multicenter trial that is designed to investigate the safety and effectiveness of a novel therapy, temporary transvenous diaphragm pacing (TTVDP), to improve weaning from MV in up to 88 mechanically ventilated adult patients who have failed at least two spontaneous breathing trials over at least 7 days. Patients will be randomized (1:1) to TTVDP (treatment) or standard of care (control) groups. The primary efficacy endpoint is time to successful extubation with no reintubation within 48 h. Secondary endpoints include maximal inspiratory pressure and ultrasound-measured changes in diaphragm thickness and diaphragm thickening fraction over time. In addition, observational data will be collected and analyzed, including 30-day mortality and time to discharge from the intensive care unit and from the hospital. The hypothesis to be tested postulates that more TTVDP patients than control patients will be successfully weaned from MV within the 30 days following randomization.

**Discussion:**

This study is the first large-scale clinical trial of a novel technology (TTVDP) aimed at accelerating difficult weaning from MV. The technology tested provides the first therapy directed specifically at VIDD, an important cause of delayed weaning from MV. Its results will help delineate the place of this therapeutic approach in clinical practice and help design future studies aimed at defining the indications and benefits of TTVDP.

**Trial registration:**

ClinicalTrials.gov, NCT03096639. Registered on 30 March 2017.

**Electronic supplementary material:**

The online version of this article (10.1186/s13063-018-3171-9) contains supplementary material, which is available to authorized users.

## Background

Mechanical ventilation (MV) is a life-saving technology routinely administered in intensive care units (ICUs). In the USA, hospitalization involving endotracheal intubation and MV increased 56% between 1997 and 2011 [1]. In 2011, MV using tracheal intubation was the third most common procedure performed in this country [1]. The proportion of ICU beds occupied by patients requiring MV on a daily basis ranges from 20.7 to 38.9% [2]. The projected costs to care for the estimated 625,000 US patients requiring prolonged MV in 2020 are expected to be $64 billion [3].

Like all active treatments, MV can be associated with several adverse effects. They include lung injury [4, 5], pulmonary infections [6], and the more recently recognized ventilator-induced diaphragmatic dysfunction (VIDD) [7–9]. VIDD most probably proceeds from MV-associated diaphragmatic inactivity or unloading, possibly aggravated by various ICU-related aggressions (sepsis, etc.). VIDD is characterized by severe muscle fiber atrophy and an array of muscle lesions [10]. The onset of diaphragm atrophy under MV is rapid, with abnormalities becoming visible histologically and functionally after only a few hours [11, 12].

Accumulating evidence suggests that VIDD is associated with delayed liberation from MV, longer ICU stays, and a higher risk of complications during the ICU stay [13]. In patients who are difficult to wean from MV, mortality increases with each additional day spent on the ventilator [14]. Animal studies suggest that keeping the diaphragm active during MV reduces VIDD development. This potential to prevent VIDD [15] remains to be established in human clinical trials, and no clinically validated cure or treatment for VIDD currently exists. Of interest, limited evidence supports the putative usefulness of inspiratory muscle training to accelerate weaning from MV in patients requiring prolonged mechanical ventilation in whom VIDD may be already present [16, 17].

Inspiratory muscle training is difficult to administer and standardize. It has therefore been proposed that pacing the diaphragm through phrenic nerve stimulation could be a solution to counteract VIDD by restoring diaphragmatic muscle mass and function, hence improving the weaning outcome [18–20]. The ability of diaphragm pacing to recondition atrophic diaphragms has long been demonstrated by studies conducted with surgically implanted stimulators in quadriplegic patients with high cervical spinal cord lesions (see recent review in [21]). In the context of “acute” MV, animal studies have shown that diaphragm pacing when superimposed on MV can mitigate the development of VIDD [22, 23]. Preliminary insights into the mechanisms responsible for this effect have also been obtained [24–26].

An absolute prerequisite for the clinical application of diaphragm pacing to overcome VIDD in the ICU is to make phrenic stimulation feasible at the bedside. Surgical techniques cannot be considered in this context. Magnetic stimulation has been proposed, but it is cumbersome [27]. Transvenous phrenic stimulation has been previously assessed in various animal models (first mentioned in reference [28]), albeit in a clinically impractical form. Recent data have shown that transvenous phrenic stimulation could be achieved in humans on a permanent basis to treat central sleep apneas [29] by means of a permanent implant. The Lungpacer LIVE® Catheter provides a technological solution to achieve temporary transvenous diaphragm pacing (TTVDP) in ICU patients through a minimally invasive bedside procedure. This system includes a proprietary intravenous multi-electrode stimulating catheter which can also deliver intravenous fluids. In the current state of the technology, a catheter is inserted in the left subclavian vein in the same way as used for a standard subclavian line. The catheter-borne electrodes provide stimulation of the left phrenic nerve as it enters the thorax posterior to the subclavian vein and stimulation of the right phrenic nerve at the level of the atriocaval junction. A first-in-human study showed that this technology delivered safe and effective diaphragm pacing [30].

The Lungpacer RESCUE 2 study (NCT03096639) tests the main hypothesis that TTVDP used in ICU patients who are difficult to wean from MV will improve the weaning outcome. Specifically, RESCUE 2 is a prospective, randomized, controlled, open-label, multicenter study with a primary objective to evaluate the efficacy of TTVDP in terms of the probability of successful weaning on day 30 using a competing risks survival model. The primary endpoint is the time to successful extubation with no reintubation within 48 h (or, in tracheotomized patients, the time to successful 24-h separation from the ventilator with no replacement on MV within 48 h). Moreover, RESCUE 2 evaluates the safety of TTVDP in the clinical context of weaning from MV.

The RESCUE 2 protocol (Revision F, as of August 31, 2018) as described in the present manuscript conforms to the Standard Protocol Items: Recommendations for Interventional Trials (SPIRIT) guidelines (http://www.spirit-statement.org/) (see Fig. 1 and Additional file 1).

**Fig. 1 Fig1:**
[figure not shown]
SPIRIT figure describing study procedures and assessments. *SOFA* sequential organ failure assessment, *RASS* Richmond Agitation-Sedation Scale, *MIP* maximal inspiratory pressure, *RSBI* rapid shallow breathing index

## Methods

### Study setting

This prospective, multicenter, randomized, controlled, open-label interventional study evaluates weaning from MV after TTVDP (treatment) or standard of care (control). In the treatment arm, in addition to standard of care, the study involves the percutaneous insertion of the LIVE® Catheter using the left subclavian approach into the superior vena cava, the capture of the left and right phrenic nerves by stimulation electrodes, and repeated daily sessions of diaphragm pacing conducted until liberation from MV. In the control arm, the study involves standard of care only, without LIVE® Catheter insertion or any kind of sham treatment (open-label design). In the trial patients will be followed until successful liberation from MV or for 30 days, whichever comes first. All study patients will be monitored for 48 h after extubation (or disconnection from MV for tracheotomized patients) and removal of the LIVE® Catheter. If a study patient is extubated on day 29 or 30, the 48 h follow-up will extend study participation out to a maximum of 32 days after randomization. All study patients will be followed to day 30 for all serious adverse events (SAEs), ICU and hospital admissions, discharges, and mortality.

Notwithstanding ulterior amendments, this study will be conducted in 10 European centers in France and Germany. These university and academic institutions are evaluating patients in a variety of ICUs as well as specific weaning units. All hospitals have established experienced research teams skilled at managing critical care patients on MV. The full list of the participating centers is provided in the Appendix.

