#### Discontinuation of therapy

The diaphragm pacing therapy sessions will be stopped when the physician determines that the patient has successfully passed the protocol-specific VLT and can be separated from the ventilator. If discontinuation of therapy occurs before the 30-day study completion, the LIVE® Catheter will not be removed until the patient has met the weaning success criterion (48 h off the ventilator).

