### Outcomes

The primary efficacy endpoint is time to successful extubation with no reintubation within 48 h. In tracheotomized patients, the primary efficacy endpoint is time to successful 24-h separation from the ventilator with no reconnection within the following 48 h.

The primary statistical analysis will model the time to event of interest, i.e., successful weaning, in the presence of competing events which include death or withdrawal of life support. The endpoint is evaluated in a competing risks survival model. In addition, withdrawal of life support and cessation of weaning in the ICU with discharge from the ICU to a specialized weaning facility by day 30 will be reported.

The secondary efficacy endpoints are:Time to first successful VLT after randomizationDifference in MIP changes between study groups from randomization to successful weaning or on day 30, whichever comes firstDifference in changes in diaphragmatic thickness (centralized blinded ultrasound evaluation) between study groups from randomization to successful weaning or on day 30, whichever comes firstDifference in changes in diaphragm thickening fraction (centralized blinded ultrasound evaluation) between study groups from randomization to successful weaning or on day 30, whichever comes firstDaily measurement of RSBI.

The safety endpoints will include characterizing the adverse event profile and comparing the nature and frequency of adverse events in patients randomized to TTVDP vs. control (standard of care) treatment. This safety assessment and the study risk management plan are described in detail within the study protocol.

Of note, additional observational data points will be collected, including (but not limited to) time to extubation, time to reintubation, time to ICU discharge, time to hospital discharge, and 30-day mortality from randomization.

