Regarding the primary efficacy endpoint (time to successful extubation without reintubation in the next 48 h), the null hypothesis states the cumulative incidence by day 30 for successful weaning is the same in patients randomized to treatment or control groups. The primary statistical analysis will be conducted on the mITT population and will model the time to the event of interest in the presence of competing events which include death and withdrawal of life support. In addition, cessation of weaning in the ICU with discharge from ICU to a specialized weaning facility will be evaluated. Patients who do not meet one of the endpoints by the end of their study follow-up will be censored at the time of study discontinuation or completion. The primary statistical model will utilize the cumulative incidence function. The event of interest, successful weaning, will be compared between randomized groups using Gray’s test. The probabilities will be summarized for successful weaning and each competing event for the duration of the study. The 95% confidence intervals will be provided for the probabilities at 30 days. In addition, descriptive statistics will be prepared by randomized group for the time to successful weaning in days.

All ITT patients will be included in the primary safety endpoint analysis. Fisher’s exact test will be used to compare the number of patients with an event or in a category of events out of the total number of patients randomized between groups as a tool to understand the adverse event profile associated with TTVDP compared to control.

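### Non-serious adverse events appear to be observed only to liberation plus 48 h, yet arms are compared on crude patient counts, so the safety comparison depends modestly on the primary efficacy event

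*Protocol article*

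**What the plan says.** Under Study setting, the article gives the general rule: "In the trial patients will be followed until successful liberation from MV or for 30 days, whichever comes first". It then adds: "All study patients will be monitored for 48 h after extubation (or disconnection from MV for tracheotomized patients) and removal of the LIVE® Catheter". For extubation on day 29 or 30, "the 48 h follow-up will extend study participation out to a maximum of 32 days after randomization". A separate sentence carries a short list of items further: "All study patients will be followed to day 30 for all serious adverse events (SAEs), ICU and hospital admissions, discharges, and mortality". Non-serious adverse events are not on that list.

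Under Outcomes, the primary endpoint is stated thus: "The primary efficacy endpoint is time to successful extubation with no reintubation within 48 h". The safety endpoints include "comparing the nature and frequency of adverse events in patients randomized to TTVDP vs. control (standard of care) treatment", without restriction to serious events. Under Statistical analysis, "Fisher’s exact test will be used to compare the number of patients with an event or in a category of events". The denominator is all patients randomised, in the intent-to-treat population, and observation time is not mentioned.

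Under Discontinuation of therapy, if pacing stops before day 30 the catheter stays in place until the patient has been off the ventilator for 48 h. Under Population size, the expected evidence is a trend in favour of pacing, together with an adverse event profile that does not differ significantly between groups.

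**The concern.** Read as written, the event that closes observation for non-serious adverse events is the event the device is meant to bring forward. A patient weaned on day 5 is observed for about 7 days; one who is neither weaned nor has a competing event is observed for 30. Counting patients with at least one event treats these windows as equal. If pacing speeds weaning, its patients have less time in which an event can be recorded, and the crude proportion falls without any change in the daily rate.

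The finding of no significant difference in adverse events is part of what the trial expects to report, and the Discussion says that the risks of pacing itself are less well defined than those of central venous catheterisation. A bias towards reassurance is the unwelcome direction here.

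The text also leaves open whether the 48 h of monitoring runs from extubation or from catheter removal. Only the treatment arm has a catheter, so the answer decides whether the tail is the same in both arms.

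**Working it through.** **Inputs.** From Population size: control 50% weaned and 34% with a competing event by day 30; pacing 80% and 11%; 44 per arm; stated power 70%. From Study setting: a 48 h (2-day) tail after liberation. Assumptions: constant hazards; a competing event ends observation; the same daily adverse event rate r in both arms. The article gives no event rate, so r runs from 0.01 to 0.10.

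**Hazards.** Total λ = −ln(1 − Fw − Fc)/30, split in the ratio Fw : Fc.
- Control: −ln(0.16)/30 = 0.0611 per day; weaning 0.0364, competing 0.0247.
- Pacing: −ln(0.09)/30 = 0.0803 per day; weaning 0.0706, competing 0.0097.

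**Check against the stated power.** Cause-specific hazard ratio 0.0706/0.0364 = 1.94. Weaning events 44 × (0.50 + 0.80) = 57.2. Schoenfeld: z = √(57.2/4) × ln 1.94 − 1.96 = 2.51 − 1.96 = 0.55, power 70.8%. This agrees with 70%, so the model is a fair reading of the plan.

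**Mean window.** (Fw + Fc)/λ + 2Fw.
- Control: 0.84/0.0611 + 1.0 = 13.75 + 1.0 = 14.8 days.
- Pacing: 0.91/0.0803 + 1.6 = 11.34 + 1.6 = 12.9 days.
- Ratio 14.75/12.94 = 1.14, which is the 14% excess in daily rate that would go unseen.

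**Proportion with at least one event.** With K = (1 − e^(−30(λ+r)))/(λ+r):
- Planned window: 1 − [(λw·e^(−2r) + λc)K + e^(−30(λ+r))]
- To day 30 or competing event: 1 − [Fw·e^(−30r) + λc·K + e^(−30(λ+r))]

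Example, control, r = 0.05, planned window: K = 8.68; (0.0364 × 0.905 + 0.0247) × 8.68 = 0.500; adding 0.036 gives 0.536, so 46.4%.

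| r per day | Planned window, control vs pacing | Difference (points) | To day 30, control vs pacing |
|---|---|---|---|
| 0.01 | 13.3% vs 11.8% | −1.5 | 20.4% vs 24.0% |
| 0.02 | 24.1% vs 21.6% | −2.5 | 36.0% vs 42.0% |
| 0.05 | 46.4% vs 42.7% | −3.7 | 63.8% vs 72.8% |
| 0.10 | 65.6% vs 62.3% | −3.3 | 81.5% vs 90.2% |

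**Fisher's test at 44 per arm, equal daily rates** (summing binomial probabilities over all tables with p ≤ 0.05). At r = 0.02, 0.05 and 0.10 the planned window rejects in 3.2%, 3.6% and 4.0% of trials. A crude comparison to day 30 rejects in 5.8%, 10.3% and 13.9%.

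**Sensitivity.**
- Competing hazard in the pacing arm set to the control value: pacing window 11.3 days, a wider gap.
- Event rate after weaning one quarter of the rate before (0.05): planned window 44.2% vs 38.9%; to day 30, 50.9% vs 50.7%.
- Tail of 96 h in the pacing arm: 11.34 + 4 × 0.80 = 14.5 days, so the average gap nearly closes.

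**The tail, text against text.** Catheter removal comes no earlier than 48 h off the ventilator. Another 48 h after removal makes about 96 h. For extubation on day 29 or 30 that would reach day 33 or 34, beyond the stated maximum of 32. Only a clock that starts at extubation fits the cap.

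**The case against.** **The window is inferred.** No sentence states the collection period for non-serious events, and the article refers to the full protocol for safety detail. That stands as a limit. But the general follow-up rule, the closed list of items carried to day 30 and the crude test are all stated; the point follows from applying them together, not from an omitted detail.

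**The data that matter most are safe.** SAEs and deaths run to day 30 in both arms, SAEs are adjudicated independently, and Fisher's test is described as a tool for understanding the profile, not as a formal safety hypothesis. This is correct and limits the point to non-serious events and to totals that include them.

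**The effect is small.** Also correct: 2 to 4 points, and Fisher's test at this size would almost never turn that into a significant result. The consequence is masking, not a false alarm.

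**Stronger readings that the documents do not support.** A reader might infer from the day-30 column (63.8% vs 72.8%) that the plan hides a 9-point excess of device harm. It does not: both arms have the same daily rate by construction, and the gap arises because fewer pacing patients are assumed to have a competing event, so they contribute more days. With a lower rate after weaning the gap vanishes. A reader might also infer that pacing patients are monitored for 96 h after extubation and controls for 48 h. The 32-day cap contradicts that; what is established is an ambiguity.

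**Conclusion.** The concern holds in a limited form. As the article reads, the observation window for non-serious adverse events ends at liberation plus 48 h, while the comparison counts patients out of all randomised. Under the plan's own rates this gives mean windows of about 14.8 and 12.9 days and about 2 to 4 points fewer pacing patients with an event at equal daily rates; a rate about 14% higher per day with pacing would look equal.

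The size rests on constant hazards, on competing events ending observation, on an assumed event rate that is the same before and after weaning, and on the 48 h tail running from extubation. The direction depends on pacing actually speeding weaning; without that effect, this mechanism produces no bias. SAEs and deaths are not affected. The point deserves correction because the expected conclusion leans on the absence of a significant difference in adverse events.

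**What to change.** 1. Keep Fisher's exact test for SAEs and deaths, which are complete to day 30.
2. Compare non-serious and all adverse events as events per observed patient-day by arm, or as cumulative incidence over a common window with death as a competing event.
3. State the collection window for non-serious events explicitly, with the same rule in both arms. Reconcile Study setting with Discontinuation of therapy on whether the 48 h of monitoring runs from extubation or from catheter removal. This concerns the observation clock only, not when the catheter should come out.

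Extending collection to day 30 and still comparing crude proportions is not enough: unequal survival would then distort the comparison, as the 5.8% to 13.9% rejection rates show.

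The per-day rate is not perfect. With a post-weaning rate one quarter of 0.05, it would be (13.75 × 0.05 + 1.0 × 0.0125)/14.75 = 0.047 in control and (11.34 × 0.05 + 1.6 × 0.0125)/12.94 = 0.045 with pacing: about 4% apart, against 44.2% vs 38.9% for crude proportions.

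Cost: wording in the analysis section, slightly more analysis and less simple adverse event tables. The per-day option needs no further data collection. Cumulative incidence to day 30 would require non-serious events to be collected after weaning, which is more work at the sites. The article says the protocol is already being amended, so the wording can go in with that revision.

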### Eligibility criteria

Prior to randomization, all study participants will undergo screening to determine eligibility. Screening evaluations will include physical examination, medical history, medication history, vital signs, weight, electrocardiography (ECG), blood tests, and arterial blood gas assessments.

Study participants will be included if they:Are at least 18 years oldAnd have been on “invasive” MV for at least 7 days (patients can be either intubated or tracheotomized; the protocol does not involve any interference with local procedures regarding the decision and timing of tracheotomy)And have failed at least two attempts at ventilator liberation, henceforth referred to as “ventilator liberation trials” (VLTs); one VLT must be the study-specific VLT (see subsequent sections); self-extubation or accidental extubation with subsequent reintubation within 48 h is considered a failed VLT.

Patients cannot be included if they:Are currently on extracorporeal membrane oxygenationHave failed weaning from MV because of current hypervolemiaHave known anatomical features preventing catheterization of the left subclavian veinHave a history of congenital heart diseaseHave clinically overt congestive heart failureAre currently being treated with a neuromuscular blockadeHave pre-existing neuromuscular diseases potentially affecting respiratory musclesHave pleural effusions occupying greater than one third of the pleural space on either sideHave a body mass index ≥40 kg/m^2^Have known or suspected phrenic nerve paralysisHave any electrical device (implanted or external) potentially prone to interaction with or interference from the temporary transvenous diaphragm pacing system, including neurological pacing/stimulator devices, cardiac pacemakers, and defibrillatorsHave been diagnosed with bacteremia (blood cultures must be negative for 48 h to consider inclusion)Have current hemodynamic instability, sepsis, or septic shockAre terminally ill with 6 months or less life expectancy or not committed to full careAre known or suspected to be pregnant or lactatingAre actively participating in another clinical trialCannot consent to participate or belong to vulnerable populations.

